#### Primary outcome measures

Mortality due to opioid intoxication in the general population in Skåne County in 2019–2023, compared with historical mortality due to opioid intoxication during 2013–2017. Number of deaths will be collected from national registries.

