#### Power and sample size

Power has been calculated only for the primary outcome measure. The total population at risk of fatal overdose in the general population is unknown, as people may be at risk of overdose death either because of a severe opioid dependence, a less severe state of dependence or a more unregular use of opioids. As the number of potentially affected individuals is unknown, the power calculations were based on numbers calculated from the number of individuals reached by the intervention at NEP and OST facilities. Thus, power calculations based on the cohort planned to receive distributed naloxone will be considered to be a minimum level with the possibility of a higher effect if the naloxone intervention disseminates also beyond the NEP and OST populations.

The number of patients in OST and NEP is estimated to comprise approximately 2000 individuals, 1000 individuals respectively. Power was calculated based on potential mortality in these two groups (calculated conservatively for 4 years prior to the intervention); a total of 4 × 2000 = 8000 person years; referred to as a ‘comparison period’), and with the conservative assumption that the intervention is calculated to reach the full study group for 1.5 years (intervention group, 2019–2020) (1.5 × 2000 = 3000 person years). The statistical power calculations are made with the Microsoft Excel sheet EPISHEET available for download at www.krothman.org/episheet.xls (downloaded on 14 January 2016).

Assuming that mortality before intervention is 50 deaths per 1000 person years in the overall cohort (that is, a 5% annual risk), a relative risk reduction of 25% (relative risk RR = 0.75) is required in order for the statistical strength to exceed 80% (81%), 5% significance limit, two-sided test, with 8000 person years before intervention (comparison period) and 3000 person years after intervention (intervention group). If however, assuming that mortality before intervention is 30 per 1000 person years in the overall cohort (that is, a 3% annual risk), a higher relative risk reduction, 32% (RR = 0.68), is required for the statistical strength to exceed 80% (81%), 5% significance limit, two-sided test, with 8000 person years before intervention (comparison period) and 3000 person years after intervention (intervention group). If the risk reduction still is 25%, even in this scenario, the statistical strength drops to 57%.

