### Statistical methods

Comparison of mortality, before and after intervention, is done by Poisson regression with an indicator variable for the intervention (0 = comparison, 1 = intervention), adjusting for age and gender distribution. The effect is described as RR (relative risk), with 95% confidence intervals. *P* values < 0.05 will be considered as statistically significant. The primary outcome measure relates to mortality in the overall cohort. The effect on mortality will be studied in OST and NEP separately, using a subgroup analysis. The evidence in effect between the cohorts will be described by the *p*-value of an interaction test. Outcomes are studied year by year during the intervention period, compared to the comparison period, year by year.

For the study aims regarding the included cohort, this is open, dynamic cohort based on individuals in OST and NEP, where they contribute with person time, as at-risk from entry to study end or death, or by possible exit from the cohort (the earliest of these three events is the end date of the personal time calculation). In the general population analyses, 2013 to 2017 constitute the comparison period, while corresponding data, during 2019–2023, constitutes the intervention period.

Each person included in the follow-up will contribute a record (row) in the research database for each year this person is included in one of the two cohorts. In the row, in addition to each individual’s consecutive number, variables such as date, sex, age, cohort (1 = OST, 2 = NEP), intervention (0 = comparison, 1 = intervention), person time, date in the event of death, and status (alive/dead) at the end of each year, will be registered. In addition, based on public registers of the number of patients in OST, in the analyses it will be possible to control for fluctuations in OST availability (number of patients in methadone and buprenorphine treatment, respectively) in the region, as OST availability is likely to affect mortality rates; for example, based on national register data from the present setting, it has been shown that the risk of overdose mortality varies depending on OST status [90].

Significance, as above, is 5%, when applying a double-sided test. The target for the statistical strength is set at 80% for primary outcome. Secondary outcome and subgroup analyses have not been calculated in strength.

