### Trial status

In July 2018, 3 weeks into the project, 70% of targeted units (*N* = 24) were included, providing OPEND and including subjects into the study. Five weeks into the project 87% of targeted units had started, after 12 weeks, all units were including patients in the project. After inclusion and establishment of the first targeted 24 units, making sure the program is well established into daily management, the naloxone project has recently included another 3 units, and are planning on further expansion. So far, reports from included units are indicating that upon completion of training, approximately 80% of patients are giving their consent to study inclusion. The intervention period begins 1 July 2019 (with the first analyses conducted for general population data for the 18-month period of 1 July 2019–31 December 2020), based on the assumption that the naloxone distribution will be considered to have reached a satisfactory level from July 2019.

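### The first general-population analysis counts July–December twice and January–June once against whole comparison years with no season term, so a half-year difference in death rates would shift the first RR, probably slightly

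*Protocol article*

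**What the plan says.** Under Trial status, the article states: "The intervention period begins 1 July 2019". The same sentence adds the "first analyses conducted for general population data for the 18-month period of 1 July 2019–31 December 2020", on the ground that naloxone distribution should have reached a satisfactory level by then.

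Statistical methods fixes the comparator: "In the general population analyses, 2013 to 2017 constitute the comparison period". It gives 2019–2023 as the intervention period. Primary outcome measures uses the same years: "Mortality due to opioid intoxication in the general population in Skåne County in 2019–2023", against 2013–2017.

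The stated model is "Poisson regression with an indicator variable for the intervention (0 = comparison, 1 = intervention), adjusting for age and gender distribution". One further covariate is offered as an option: "it will be possible to control for fluctuations in OST availability". The section also says: "Outcomes are studied year by year during the intervention period, compared to the comparison period, year by year".

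The article nowhere mentions seasonality, and it gives no monthly or half-yearly death counts.

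**The concern.** A person-time offset corrects for the different length of the two periods. It does not correct for a different mix of calendar months. In the first analysis two thirds of the intervention time falls in July–December, against one half of the comparison time. If deaths run at a different rate in the two halves of the year, that difference enters the intervention coefficient.

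The study rests on a before/after contrast in one region. The article's section on opioid overdose mortality in Sweden itself warns that death counts fluctuate and make interventions hard to judge. An avoidable calendar artefact should not be added to the first published RR. If January–June is the heavier half, the artefact looks like benefit. If July–December is heavier, it hides benefit.

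**Working it through.** **Inputs from the article.** Intervention window 1 July 2019–31 December 2020 (Trial status). Comparison years 2013–2017 (Primary outcome measures; Statistical methods). National drug-related death rate 92 per million (Opioid overdose mortality in Sweden). About 1.3 million inhabitants (Setting).

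**Assumptions.** Let s be the July–December share of yearly deaths, not given in the documents and taken as 0.45 to 0.55. Let d = 2s − 1 be the deviation of the July–December rate from the yearly mean. The seasonal pattern is taken as the same in all years, and the halves as equal in length. For precision only, yearly deaths are taken as 92 × 1.3 ≈ 120. This is a national, all-drug rate applied to the region.

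**Plan's own figures.** For 8000 against 3000 person-years, two-sided 5%, a two-proportion calculation with pooled variance gives:

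| Baseline per 1000 | RR | Stated power | Recomputed |
|---|---|---|---|
| 50 | 0.75 | 81% | 80.6% |
| 30 | 0.68 | 81% | 80.5% |
| 30 | 0.75 | 57% | 57.0% |

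The figures reproduce and are not in question.

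**Null RR of the 18-month analysis.** In units of one year's deaths, the window expects 2s + (1 − s) = 1 + s over 1.5 years. Whole years expect 1 per year. So null RR = (1 + s)/1.5 = 1 + d/3.

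| s | d | Null RR |
|---|---|---|
| 0.45 | −0.10 | 0.967 |
| 0.48 | −0.04 | 0.987 |
| 0.52 | +0.04 | 1.013 |
| 0.55 | +0.10 | 1.033 |

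**Size against sampling error.** Comparison deaths are 5 × 120 = 600 and intervention deaths 1.5 × 120 = 180. SE(log RR) = √(1/600 + 1/180) = 0.085. At s = 0.55, ln(1.033)/0.085 ≈ 0.39 SE, and the two-sided 5% error becomes about 6.7%. At s = 0.52 it is about 5.3%. At a 60:40 split (s = 0.60), the null RR is 1.067 and the error about 12%.

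**Longer windows.** From 1 July 2019 to 31 December 2023 there are five July–December and four January–June halves. The null RR is (5s + 4(1 − s))/4.5 = 1 + d/9, which is 1.011 at s = 0.55. With whole years 2019–2023 it is 1.00.

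**Year-by-year results.** If 2019 contributes July–December only, its rate against whole years has null RR 2s = 1 + d: 0.90 at s = 0.45 and 1.10 at s = 0.55. That is three times the shift in the 18-month result.

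**With a half-year factor.** Both periods consist of complete half-years, so the factor returns the null RR to 1.00 for a pattern that is stable over years. At s = 0.5 the strata hold 300 and 60 deaths (January–June) and 300 and 120 (July–December). Information is 1/(1/300 + 1/60) + 1/(1/300 + 1/120) = 50 + 85.7 = 135.7, so SE = 0.086 against 0.085 without the factor. On the plan's person-years (50 per 1000, RR 0.75), Wald power on the log RR goes from 76.9% to 76.1%.

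**Month-matched 18-month windows.** Only two non-overlapping windows running from July to December of the next year fit in 2013–2017, for example July 2013–December 2014 and July 2015–December 2016. They use 36 of 60 months, so 3 × 120 = 360 deaths, and SE = √(1/360 + 1/180) = 0.091.

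**The case against.** The strongest reply is that nothing in the documents shows a seasonal pattern, so the bias is hypothetical. Even at the ends of the assumed range it is about 3%, beside the 25–32% reductions used in the power section. This stands, and it limits the point to a minor one.

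A second reply is that matching of months for an early look belongs in the analysis plan, which is not shown. Trial status does not say which comparison months the first analysis uses. That is fair in part: the analysis plan may already handle it. But the article itself fixes the window, the comparison years and the core covariates, and together they do not balance the halves.

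Three stronger readings are tempting, and the documents do not support them.

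- A reader might infer that the powered analysis is biased, because the power section assumes the intervention will "reach the full study group for 1.5 years (intervention group, 2019–2020". The length and years match, but that calculation concerns OST and NEP cohort person-years, uses a four-year comparison and names no months. Trial status speaks of general-population data.
- A reader might infer that any seasonal pattern distorts the result. Only a January–June versus July–December contrast does, and one third of it enters the RR. Patterns that average out within each half cancel.
- A reader might infer that the main 2019–2023 comparison is biased. As whole years it is balanced. If the July 2019 start is carried through, one ninth of the deviation remains.

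**Conclusion.** The point holds for the first general-population analysis. As stated, that analysis compares an 18-month window weighted towards July–December with whole calendar years and makes no adjustment for season. The null RR is (1 + s)/1.5, or 0.967 to 1.033 for an assumed July–December share of 0.45 to 0.55. Under the further assumption of about 120 deaths a year, this is at most about 0.4 SE and an error rate near 7%. A more uneven split would make it material. The direction is unknown. It is a small, avoidable weakness in one early result. A half-year 2019 result in the year-by-year comparison is more exposed. Separately, the 1 July 2019 start and the 2019–2023 intervention period disagree on their face, and that choice decides whether any imbalance remains in the final analysis.

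**What to change.** For the 18-month analysis, split deaths and person-time in both periods into half-years and add a January–June/July–December factor to the Poisson model. Do the same for any year-by-year result in which 2019 covers July–December only. The cost is 1 degree of freedom and under one percentage point of power. No comparison data are discarded. Deaths come from registers, and the date of death is already a planned variable in the cohort database. The general-population counts need to be extracted by half-year.

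Month-matched 18-month comparison windows are not an equal substitute. They discard 24 of the 60 comparison months and raise the SE from about 0.085 to 0.091, against about 0.086 with the factor. Overlapping windows would count deaths twice.

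Also state whether the 2019–2023 comparison begins on 1 January or 1 July 2019, and make Trial status, Primary outcome measures and Statistical methods agree. If it begins on 1 July, keep the half-year factor in the final model too.

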## Discussion

This report describes the development, design and implementation of a regional, multi-site OPEND program in South Sweden, with the purpose to study the effects of a Naloxone distribution program in Skåne County. Building on existing infrastructure as a basis for the implementation was crucial, in order to manage rapid and safe implementation and expansion, targeting units reaching populations with highest risk for opioid overdoses, such as NEPs and OST clinics and units treating inpatients at high risk. Within 3 weeks 70% of targeted units were up and running and had started training patients. Within 12 weeks, all of the units were serving as OPEND units, including subjects to the study. Results are hypothesized to demonstrate the feasibility of implementing the first large scale OPEND in Sweden and to demonstrate an effect on population-based rates of opioid-related mortality from a large-scale naloxone distribution program.

### Opportunities and challenges

The unique infrastructure in the region makes Skåne County an interesting setting for implementation of a large scale naloxone program. From any town in the region, there is a possibility to access any of the four NEP’s or any of the 18 OST clinics within a maximum of one and a half hour by public transport. Although this setting is not found elsewhere in Sweden, this protocol, alongside all the education and information material produced in order to implement this project, shared on the project homepage [93], increases the ability for others to reproduce the study in another setting.

Distributing naloxone by and to peers and family members is not yet possible in Sweden, due to legislation, however training is. Increasing knowledge and awareness is a large part of making a change in the dark trends of high rates of overdose related deaths in Sweden. The goal set by the naloxone project, to educate all patients in OST and all patients visiting NEP, is high. However, if everyone who has the opportunity to obtain a kit does so and inform friends and family where they keep it, how to recognise and respond to an overdose, then there is a possibility to make a change. Naloxone projects offer the opportunity of actively working with attitudes and awareness connected to stigma as it depends on the collaboration between public health and the expert (the patient/user) [94], which has been found to increase empowerment among users [75].

The lack of formal THN programs to family members may be discussed as a potential limitation in future scientific publications from the project. Also, future documentation will assess and discuss the question of possible naloxone availability prior to study start, although this is suspected to be very low and likely to be close to negligible, as naloxone prescription became legal only soon before the project started.

In addition, further discussions in future publications can address if the settings included in the study, OST facilities, NEP facilities and emergency and detoxification wards in an addiction clinic, reach the full population of people with harmful use of opioids with risk of overdose. The NEP of the major city in the area, Malmö, has been described to reach around 70% of people who inject drugs in the catchment area of that facility [86], although such approximations are clearly difficult to make. However, OST and treatment centres also reach opioid-dependent subjects who do not inject. In addition, the future documentation of the study will address the limitation that individuals with prescription drug use on a level that does not cause any treatment or harm reduction contact may still be difficult to reach. Thus, all in all, it cannot be established how large the population at risk of overdoses in the region may be.

In relation to international targets, the absolute minimum annual naloxone distributed rate, should ideally be 9 to 20 times that of fatality rates, in order to prevent opioid overdose death [95]. Findings from research in Massachusetts suggest distribution of naloxone is dose related as the greatest reductions in opioid related deaths were seen in areas where distribution exceed 100 THN kits per 100,000 inhabitants [17]. Reaching all individuals at risk is certainly pivotal in order to efficiently fight drug related mortality and morbidity in the region, but this also relies on the same individuals to carry naloxone when there is a need for it. Self-reported carriage rate in the pilot study of N-ALIVE in the first 4 weeks after prison release was 71% [96]. Results from the national Scottish naloxone program show that even if there was a significant increase in prescriptions of naloxone, among participants accessing needle exchange services, disturbingly enough reported numbers on carriage showed a significant decrease over the same period, from 16 to 5 % [97]. A recent study in Norway, covering six cities with THN, showed 57% of subjects, recently reported heroin injection, currently carrying naloxone [98], numbers witnessing of a high degree of saturation. Differences in how carriage is defined should be taken into consideration, since this partially explain variations. Thus differences in actual carriage, and what motivates or discourages individuals to carry naloxone, needs to be further investigated.

Naloxone training provides the opportunity to increase knowledge and attitudes [73], shifting from sometimes dangerous and inappropriate folklore actions, to appropriately responding to opiate overdoses [99]. Increase of knowledge and attitude is also an important step in overdose prevention as false beliefs can have devastating consequences, such as high-risk individuals not perceiving themselves as being at risk [100]. The same remedy should be used for a constructive dialogue when responding to fears on over-antagonism [101] and fear of police involvement when calling the ambulance services [102–104]. Research shows that even after implementation of Good Samaritan Law, study participants still feared repercussions when calling ambulance services [102], while an overwhelming majority of participants from another study reported positive experiences of dealing with police and paramedics [105]. Real, or perceived as real, fears should be taken seriously as consequences of being controlled by fears can result in harm or, in worst case, death.

Though project funds cover all material and reimbursement for the naloxone spray, the project do not allocate additional resources or finances for compensation for time lost due to workforce training of colleagues and patients. Another challenge related to staffing was the decision to start implementation at the same time as the beginning of summer holidays. However, the priority was to get naloxone out on the streets as fast and as efficiently as possible. Waiting for a better opportunity would most likely equal a waste of valuable time to save lives.

## Data Availability

The datasets used and/or analysed during the current study are available from the corresponding author on reasonable request, provided this is compliant with national legislation and with the decisions of the Swedish ethics committee.

## Abbreviations

CPR: Cardiopulmonary Resuscitation
e-CRF: electronic Case Report Form
FDA: Food & Drug Administration, United States
ICD: International Classification of Diseases
ICH GCP: International Conference on Harmonisation Good Clinical Practice
ITT: Intention To Treat
NA: Not applicable
NEP: Needle Exchange Program
NK: Not known
OPEND: Overdose Prevention Education and Naloxone Distribution
OST: Opioid Substitution Therapy
RLS: Reaction Level Scale
RR: Relative Risk
THN: Take-Home Naloxone
